# Opioid reduction and enhanced recovery in orthopaedic surgery (OREOS): a protocol for a feasibility randomised controlled trial in patients undergoing total knee arthroplasty

**DOI:** 10.1186/s40814-024-01457-9

**Published:** 2024-02-15

**Keywords:** Persisting pain, Feasibility, Opioid reduction, Knee arthroplasty, Multicomponent intervention

## Abstract

**Background:**

Knee arthritis is a leading cause of limited function and long-term disability in older adults. Despite a technically successful total knee arthroplasty (TKA), around 20% of patients continue to have persisting pain with reduced function, and low quality of life. Many of them continue using opioids for pain control, which puts them at risk for potential long-term adverse effects such as dependence, overdose and risk of falls. Although persisting pain and opioid use after TKA have been recognised to be important issues, individual strategies to decrease their burden have limitations and multi-component interventions, despite their potential, have not been well studied. In this study, we propose a multi-component pathway including personalized pain management, facilitated by a pain management coordinator. The objectives of this pilot trial are to evaluate feasibility (recruitment, retention, and adherence), along with opioid-free pain control at 8 weeks after TKA.

**Methods:**

This is a protocol for a multicentre pilot randomised controlled trial using a 2-arm parallel group design. Adult participants undergoing unilateral total knee arthroplasty will be considered for inclusion and randomised to control and intervention groups. Participants in the intervention group will receive support from a pain management coordinator who will facilitate a multicomponent pain management pathway including (1) preoperative education on pain and opioid use, (2) preoperative risk identification and mitigation, (3) personalized post-discharge analgesic prescriptions and (4) continued support for pain control and recovery up to 8 weeks post-op. Participants in the control group will undergo usual care. The primary outcomes of this pilot trial are to assess the feasibility of participant recruitment, retention, and adherence to the interventions, and key secondary outcomes are persisting pain and opioid use.

**Discussion:**

The results of this trial will determine the feasibility of conducting a definitive trial for the implementation of a multicomponent pain pathway to improve pain control and reduce harms using a coordinated approach, while keeping an emphasis on patient centred care and shared decision making.

**Trial registration:**

Prospectively registered in Clinicaltrials.gov (NCT04968132).

## Background

Arthritis is a very common and painful joint condition affecting 6 million Canadians, and nearly 1 in 2 Canadians over the age of 65 [1, 2]. Osteoarthritis (OA) is the most common form, affecting more people than all other forms of arthritis combined [2]. End-stage knee OA is treated by total knee replacement (also known as total knee arthroplasty; TKA), which results in substantial improvements in pain and functional outcomes for most people. TKA is the second most common surgery in Canada with > 75,000 procedures performed in Canada in 2018–2019 [3, 4]. Although TKA is considered to be a successful treatment, around 20–25% of patients have lasting pain after surgery [5, 6]. Chronic post-surgical pain (CPSP) is complex, and factors known to be associated with it include pre-operative psychological factors like anxiety, depression and pain catastrophizing; pre-existing chronic pain and opioid use; and the severity and duration of postoperative pain [7–10]. Among patients who develop CPSP after TKA, 56% of them continue use of opioid analgesics at 30 days after surgery, 40% after 4 months and 25% after 2 years [11–13]. The traditional approach to post-discharge pain management has been for orthopaedic surgeons to prescribe a set number of institutionally standardized pain management medications, which can include non-steroidal anti-inflammatory drugs (NSAIDs) and/or opioids, without accounting for individual pain trajectories and preferences. However, studies have suggested that distinguishing problematic pain resolution from normal resolution may not be possible unless we appreciate individual patterns over time by personalized assessment and management following TKA [14].

Opioids are an important part of perioperative pain management [15–17]. However, their potential for long-term adverse effects such as persistent opioid use (POU) [18], addiction and dependence, overdose, diversion of unused pills [19, 20] and death in severe cases are well recognized [15, 21]. Preoperatively, one-third of patients in Canada with end-stage knee OA use prescription opioids [22]. Based on a large database study of 69,368 arthroplasty patients, 13% of opioid-naive and 62% of chronic opioid users continued their opioid use at 1 year after TKA [23]. Patients using preoperative opioids are particularly at risk of POU; 64 to 77% of chronic opioid users continue to use opioids after surgery, particularly after arthroplasty [24, 25]. In general, reducing opioid prescriptions can certainly help as not all patients may need opioids [25–27]. However, limiting opioids without individualizing the treatment of persistent pain can potentially drive patients to illicit sources.

A recent scoping review identified 141 studies to decrease opioid use in orthopaedic surgery, of which 70 were in the arthroplasty field (49.6%). Only 8.5% (12/141) of studies followed patients beyond 7 days, only four had follow up of three or more months, further only 24% of TKA studies used multimodal interventions. None of them had a preoperative education and risk reduction component. Important findings included were (1) both preoperative pain and preoperative opioids independently increase the risk of persistent pain and chronic opioid needs [10, 23, 24, 28, 29]. Despite this, most studies have excluded such patients, thereby limiting the external validity [30]; (2) most studies are associated with attempts to achieve in-hospital opioid free care [31, 32], which has not been shown to influence long term opioid use [17]; (3) most studies have focused on single interventions with limited or no effect [33, 34]; (4) the majority of studies involve a follow-up duration of a few weeks or less [30, 31, 34]; and most importantly, (5) existing trials do not take into account the individual variability within patients for pain resolution [35].

Perioperative surgical home (PSH) care pathways are defined by the American Society of Anesthesiologists as ‘patient-centred and physician-led multidisciplinary and team-based system of coordinated care that guides the patient throughout the entire surgical experience’. Over the last decade or so, several publications have highlighted its potential role in overcoming problems at the population level by providing a system that provides coordination during all phases of surgery [36]. Despite this, a recent (2020) systematic review on PSH demonstrated only low evidence for studies supporting its use [37]. Similarly, there are no randomised controlled trials (RCTs) on transitional pain clinic approaches, which have become conceptually very popular and are currently being used in many centres [38]. Based on the literature, we identified the need of four components that form the core of our care pathway/intervention arm; (1) patient education and expectation setting, (2) identification and modification of preoperative risk factors, (3) personalized analgesic prescriptions and (4) continued support for pain control and recovery.

Before embarking on a larger trial, we plan to assess the feasibility of implementing a multicomponent pain management pathway with the use of a pain management coordinator at each site. We believe that if the results of this trial deem feasible, the definitive trial will allow for the implementation of a coordinated approach to care, to improve pain control and reduce harms, while also emphasizing patient centred care and shared decision making.

## Objectives

The principal objective is to assess the feasibility of conducting a larger randomised controlled trial (RCT) of a multicomponent care pathway versus standard care to improve pain control and decrease opioid use in TKA patients.

### Feasibility objectives

The feasibility objectives will be to evaluate adherence to the study intervention, participant recruitment and participant retention. We will observe any challenges in implementing the study interventions and data collection procedures to consider appropriate changes to the final design.

### Clinical objectives

The clinical objectives will be the objectives of the definitive trial. The primary objective for the definitive trial will be to assess the effect of the multicomponent interventional pathway on opioid free pain control at 8 weeks after TKA versus standard care. We define opioid free pain control as a state of good pain control (three consecutive days of < 4/10 average pain score on a 0–10 numerical rating scale [NRS] with no opioid use for the operated knee). Other objectives include evaluating:Presence of CPSP at 3, 6, 9 and 12 months [39]Presence of POU at 3, 6, 9 and 12 monthsAverage intensity of CPSP at rest and with movement at 3, 6, 9 and 12 monthsSatisfaction with pain control at 3, 6, 9 and 12 monthsReturn to function at 3, 6, 9 and 12 monthsKnee function at 3, 6, 9 and 12 monthsQuality of life at 3, 6, 9 and 12 monthsOperative and knee-related complications during the studyEconomic analyses

## Methods

### Overview of the design

This is a multicenter pilot randomised controlled trial using a 2-arm parallel group design (Fig. 1). For the pilot trial, we aim to recruit participants from three high volume arthroplasty hospitals in Ontario. If the definitive trial proceeds with no major methodological changes, we will include the pilot trial patients in the definitive trial.

**Fig. 1 Fig1:**
[figure not shown]
OREOS interventional pathway

### Patient selection

All patients who are being scheduled for primary elective TKA will be screened for eligibility by participating surgeons (target approximately 1–6 weeks before surgery). We will aim to include proportions of men and women in our trial that are representative of the TKA population. We will record numbers of ineligible patients and those who decline to participate. The surgeon or their delegate will inform potentially eligible patients by phone or in person to invite them to speak with the research coordinator about the trial. Each institution will determine their own recruitment processes based on local research ethics board (REB)-approved practices. Sites will be allowed to select an informed consent method that meets their REB and local institutional guidelines. This could include written informed consent or verbal consent. The informed consent process will be documented in all cases.

### Eligibility criteria

Inclusion criteria:Adult (18 +)Undergoing elective TKA for knee arthritisCan use a simple electronic device (phone or tablet)Provide informed consent to participate

Exclusion criteria:Revision surgerySimultaneous bilateral arthroplastiesUnable to consent (e.g. cognitive disability or substantial language barrier without a support person)

### Interventions

#### Intervention group

Participants will participate in a multicomponent pathway coordinated by a trained pain management coordinator who will facilitate patient participation and engagement with each interventional component (Fig. 2). Study interventions will start 1–6 weeks before their surgery. In the intervention group, patients will participate in study interventions through their preoperative, in-hospital, and post-operative period, up to two months after their surgery.

**Fig. 2 Fig2:**
[figure not shown]
Schematic of the study intervention

Intervention participants will be stratified into high risk or standard risk based on preoperative opioid use, depression, anxiety and/or kinesiophobia by the pain management coordinator. The pain management coordinator will then facilitate the delivery of preoperative components of pain education (all intervention participants) and cognitive behavioural skill (CBS) sessions for high-risk patients (based on cognitive behavioural therapy [CBT] principles); and post-operatively, the coordinator will facilitate personalized analgesic prescriptions, and check in with patients about pain control and functional recovery. This role can be fulfilled by any health care personnel who can be trained to deliver patient education and conduct CBS sessions (e.g. medical graduate, allied health professional). All intervention components will be standardized and protocolized in an intervention manual. Study outcomes will be collected by separate research personnel not involved in the patient’s clinical care.

Pre-operatively, participants will view pre-recorded online presentations on ‘understanding pain after surgery’ and ‘managing pain after surgery’ developed by a pain physician in collaboration with a psychologist, occupational therapist and physiotherapist. Educational content includes simple pain physiology, surgical pain experience and resolution, setting expectations, goals of functional pain relief, managing daily activities and opioid benefits and risks. The coordinator will facilitate and encourage participants’ access to these online modules and will answer participants’ questions.

The pain management coordinator will conduct preoperative risk assessments based on preoperative opioid usage, depression, anxiety and kinesiophobia. Participants who meet one or more of the high risk criteria will be asked to complete two sessions of CBS sessions and suggestions on opioid sparing strategies (in-person or virtual) [7, 28, 40]. Preoperative opioid use increases the risk of poor outcomes. If the participant is considered high risk for opioid use and is willing to reduce their opioid use, the pain management coordinator will work with the site pain physician to safely reduce their opioid use. Very few opioid reduction studies focus on high-risk populations, so the evidence behind identification of individual risk components and preoperative risk education is lacking. However, this strategy is recommended by the American Society of Enhanced Recovery [28].

Post-discharge, patients will have scheduled virtual/telephone check-ins with the pain management coordinator before hospital discharge and at 1, 2, 3, 4, 6 and 8 weeks after surgery (total 7 check-ins). During these meetings, the coordinator will deliver continued support for pain control and recovery, and personalized analgesic prescriptions. The pain management coordinator will encourage the use of non-opioid analgesics and non-pharmacological measures (e.g. exercise, mindfulness, ice) [41] and encourage safe use of opioids where appropriate. The coordinator will also answer questions and facilitate virtual or in-person meetings with the surgical team if problems arise. Patients who are willing to reduce their opioid use will be supported to slowly wean their opioids, with the support of a pain physician. Based on a study assessing guided opioid tapering support, patients were able to successfully reduce/discontinue their opioid consumption following TKA [42]. Therefore, we believe that many patients will be enthusiastic about post-operative opioid tapering and discontinuation if their knee pain has been controlled by TKA.

The pain management coordinator will facilitate individualized discharge prescriptions integrating patient preferences. For example, some patients prefer not to use opioids because they have experienced adverse effects in the past, while others feel that opioids work well for them. Some patients would like to try non-pharmacological pain management strategies such as exercise or cold therapy.

#### Control group

All patients will receive usual care at their center. Presently, this does not include a pain management coordinator. Existing pre-operative knee classes at enrolling sites are not typically oriented towards pain education and appropriate opioid use. Post-operative discharge medications vary according to surgeon’s preference and are not typically individualized to patients’ needs. The research personnel will follow all participants for study outcomes.

#### Perioperative care and surgical treatment

Participants will undergo usual perioperative and surgical care at their centre. Choice of surgical technique, anesthetic technique, and in-hospital analgesia will be left to the treating surgeon, anaesthesiologist, and allied health team. Individual analgesic components in-hospital have not been shown to influence post-discharge outcomes such as POU or CPSP in larger studies [17].

### Study outcomes

#### Primary (feasibility) outcomes and criteria for success

Feasibility outcomes include intervention adherence, participant recruitment and participant retention (Table 1). We will note the percentage of participants receiving at least 3 of the 4 trial intervention components. We will consider > 90% as feasible; 80–90% to consider design modifications; and 80% as not feasible. Adherence to the intervention will be captured using an adherence checklist by the coordinator. The following criteria must be met to consider that the intervention components were adhered to for each patient: (1) patients must have reviewed both preoperative educational modules and 2 sessions of cognitive behavioural skills if in the high risk group; (2) coordinator must have stratified the patient into high or standard risk; (3) the surgeon must have provided a personalized discharge prescription, facilitated by the coordinator; and (4) the patient and coordinator must have connected in person or virtually for at least 6 of the 8 scheduled post-operative check-ins. We aim to recruit 100 patients in 4 months. We will consider > 90% participant retention to be feasible at 12 months post-operatively, 80–90% to consider design modifications and < 80% is not feasible. Table 2 shows the criteria for success of feasibility objectives.

**Table 1 Tab1:** Trial objectives, outcomes and analyses

***Feasibility objectives***	***Feasibility outcomes***	***Evaluation metrics***	***Analysis***
Intervention adherence	Percentage of patients receiving at least 3 of the 4 trial intervention components	> 90% feasible; 80–90% to consider design modifications; < 80% not feasible	Descriptive
Patient recruitment	Time to recruit target sample size	We aim to recruit 100 patients in 4 months	
Patient retention	Percentage of follow up at 12 months	> 90% feasible; 80–90%-consider design modifications; < 80%-not feasible	
***Clinical Objectives***	***Clinical outcomes***		***Analysis***
Opioid-free pain control	Time to three or more consecutive days of < 4/10 pain score on a 0–10 NRS with no opioid use for the operated knee		hazard ratios, 95% CI; Kaplan–Meier survival curve
Presence of chronic postsurgical pain (CPSP) at 3, 6, 9 and 12 months	Presence of CPSP as adopted in the International Classification of Diseases (ICD)-11 version by World Health Organization		descriptively as point estimates and 95% CI by group, with minimally important differences presented for context
CPSP pain intensity at rest and movement	Average pain score over the previous week in 0–10 NRS		
Presence of persistent opioid use (POU)	Presence of daily opioid use, started after surgery or increased after surgery (binary)		
Satisfaction with pain control at 3, 6, 9 and 12 months	Using a 0 to 100 scale (0 = extremely dissatisfied, 100 = extremely satisfied)		
Return to function at 3, 6, 9, and 12 months	Using the Return to Function questionnaire		
Knee function at 3, 6, 9 and 12 months	Using Oxford Knee Scale (OKS)		
Quality of Life	Using Euro-Qol 5 Dimensions (EQ-5D) instrument		
Economic analysis	Intervention costs and healthcare resource utilization information as well as information on productivity (e.g. time missed from work) will be collected using a self-administered questionnaire, developed for the purpose of this study		QALYs associated with each study arm will be reported as point estimates along with confidence intervals but not compared in a formal economic evaluation
Complications	Surgery-related and knee-related adverse events, pain medication related adverse events, readmissions, and serious adverse events (SAEs)		descriptively by group

**Table 2 Tab2:** Feasibility criteria and determining success

Feasibility criterion	Proceed	Proceed with modifications	Do not proceed/major modifications
Adherence (at least 3 of 4 components)	> 90% of participants	80–90% of participants	< 80% of participants
Recruitment	100 participants in 4 months	100 participants in 4–12 months	< 100 recruited or > 12 months
Retention	> 90% of participants	80–90% of participants	< 80% of participants

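### The adherence rule scores component 2 on risk stratification alone and counts the CBS sessions under component 1, contrary to the protocol's own definition, so it can only raise adherence among stratified high-risk participants

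*Protocol article*

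**What the plan says.** The Abstract (Methods) names component 2 "preoperative risk identification and mitigation". The Background lists it, among the four core components, as "identification and modification of preoperative risk factors". Under Interventions, the coordinator stratifies all intervention participants by risk, and those found to be high risk are asked to attend two CBS sessions.

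The section Primary (feasibility) outcomes and criteria for success takes as its adherence measure the "percentage of participants receiving at least 3 of the 4 trial intervention components" and sets one criterion for each component:

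- Component 2 rests on a single staff action, namely that the "coordinator must have stratified the patient into high or standard risk".
- Component 1 carries the CBS requirement as well as education, in these words: "patients must have reviewed both preoperative educational modules and 2 sessions of cognitive behavioural skills if in the high risk group".
- Component 3 is an individualised prescription from the surgeon at discharge, arranged with the coordinator's help.
- Component 4 is a minimum number of contacts with the coordinator after surgery, six out of eight.

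On recording, it states: "Adherence to the intervention will be captured using an adherence checklist by the coordinator". Table 2 turns the result into a decision: above 90% proceed, 80–90% proceed with modifications, below 80% do not proceed or make major modifications.

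**The concern.** Component 2 as defined has two parts, finding the risk and doing something about it. Component 2 as scored has only the first. The second part, which for high-risk participants includes the CBS sessions, is bundled with education, so missing both the modules and CBS costs one component rather than two. The 3-of-4 rule forgives one missed component.

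Adherence is one of three criteria that decide whether a definitive trial goes ahead, possibly with the pilot participants included. The Background stresses that earlier studies lacked preoperative education and risk reduction. A high-risk participant can receive neither in full and still count towards a favourable decision.

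**Working it through.** **The plan's own figure.** The only adherence calculation in the article is under Sample size determination: 90 of 100 adherent gives a lower confidence bound above 80%. The Wald bound is 0.90 − 1.96 × √(0.90 × 0.10 / 100) = 0.841; Wilson gives 0.826 and Clopper-Pearson 0.824. The statement reproduces. It does not bear on how a participant comes to be counted as adherent, which is the point here.

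**Where the two scorings differ.** For a stratified high-risk participant let E = both modules reviewed, C = both CBS sessions completed, P = personalised prescription, S = check-in criterion met.

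- Current rule: criterion 2 is met, so adherence needs at least 2 of {E and C, P, S}.
- Aligned rule (CBS moved to component 2): at least 3 of {E, C, P, S}.

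Over all 16 patterns the two disagree on one: E = 0, C = 0, P = 1, S = 1. The current rule passes it and the aligned rule fails it. For standard-risk participants C does not apply and the rules are identical. This step needs no assumed rates.

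**Size.** The article gives no completion rates, no dependence between items and no high-risk share. Assume each of E, C, P and S is met with probability p, and that P and S are independent of each other and of E and C. The gap among high-risk participants is Pr(E = 0, C = 0) × p²:

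- E and C independent: (1 − p)² × p²
- E and C always fail together: (1 − p) × p², the largest gap possible under these assumptions

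At p = 0.80:

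- Independent: current 0.64 + 0.64 × 0.32 = 84.5%; aligned 4 × 0.8³ × 0.2 + 0.8⁴ = 81.9%; gap 0.04 × 0.64 = 2.6 points.
- Together: current 0.64 + 0.80 × 0.32 = 89.6%; aligned 0.80 × (1 − 0.04) = 76.8%; gap 0.20 × 0.64 = 12.8 points.

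| p | High-risk gap, independent | High-risk gap, together | Whole arm, 50% high risk (assumed) |
|---|---|---|---|
| 0.70 | 4.4 | 14.7 | 2.2 to 7.4 |
| 0.75 | 3.5 | 14.1 | 1.8 to 7.0 |
| 0.80 | 2.6 | 12.8 | 1.3 to 6.4 |
| 0.85 | 1.6 | 10.8 | 0.8 to 5.4 |
| 0.90 | 0.8 | 8.1 | 0.4 to 4.1 |

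At p = 0.80 the whole-arm gap is 0.6 to 3.2 points with 25% high risk and 1.9 to 9.6 points with 75%.

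**Effect on the decision, 50% high risk.** At p = 0.85 standard-risk participants score 93.9% under either rule.

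- Independent: current (93.9 + 90.7)/2 = 92.3%; aligned (93.9 + 89.0)/2 = 91.5%. Both mean proceed.
- Together: current 93.9%; aligned (93.9 + 83.1)/2 = 88.5%. The decision moves to proceed with modifications.

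At p = 0.75 with independence the figures are 80.9% and 79.1%, on either side of the 80% line, but only because the rate happens to sit there.

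**The case against.** The strongest reply is that this is largely a labelling matter. CBS is not left unscored: it is compulsory within criterion 1 for high-risk participants, which makes that criterion harder for them. The Interventions section itself presents education and CBS together as preoperative components. The tolerance for one missed component comes from the 3-of-4 threshold, which is the investigators' choice. Under independence the gap is small. All of this stands and limits the size, but it does not remove the conflict between the definition and the scoring, nor the pattern that passes because of it.

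Two stronger readings are tempting.

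- A reader might infer that component 2 is automatic, so that 3 of 4 is really 2 of 3, and measure the overstatement as 89.6% against 81.9% at p = 0.80, or 93.9% against 89.0% at p = 0.85. The documents do not support this. Stratification is planned for everyone, but no completion rate is given, and it rests on assessing opioid use, depression, anxiety and kinesiophobia in a limited preoperative window, so it can be missed. The comparison is also with a hypothetical rule of four equally demanding components. Realigning CBS does not produce that rule, since standard-risk participants are still scored on stratification alone.
- A reader might infer that the misplacement by itself lets the pilot proceed with CBS undelivered. It does not. A high-risk participant who misses only CBS passes under both wordings, through modules, prescription and check-ins (and, at present, stratification).

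**Conclusion.** The concern holds in limited form. The scoring of component 2 contradicts the protocol's own definition, and among stratified participants the consequence runs one way only, towards a higher adherence figure. That much rests on the text alone.

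The size rests on assumptions. At p = 0.80 it is about 2.6 points among high-risk participants if module and CBS failures are independent, and 12.8 if they coincide. Over the arm, with half assumed high risk, it is 1.3 to 6.4 points. Some joint failure is plausible, because both are tasks asked of the participant before surgery, but the article offers no data on it. A general claim that the decision would change is not supported: at p = 0.85 and 50% high risk the change needs joint failure (93.9% against 88.5%). Under independence at that p, the aligned figure drops below 90% only when about 80% or more of the arm is high risk. The point is worth correcting because it affects a primary progression criterion and the correction is nearly free.

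**What to change.** Reword the adherence checklist. Component 1 is met when both education modules have been reviewed. Component 2 is met when the participant has been risk stratified and, if high risk, has completed both CBS sessions. Keep components 3 and 4, the 3-of-4 rule and the bands in Table 2.

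Rewording alone still passes a high-risk participant who misses only CBS. So also report, alongside the progression decision, the percentage meeting each component and CBS completion among high-risk participants, with confidence intervals as for the other feasibility outcomes.

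The cost is a wording change and a few descriptive lines. The current criteria already require the same items to be recorded, and no care changes. The downside is that the adherence figure may come out slightly lower.
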